## Abstract

**Background:**

Cardiac rehabilitation has beneficial effects on morbidity and mortality in patients with coronary artery disease, but is vastly underutilised and short-term improvements are often not sustained. Telerehabilitation has the potential to overcome these barriers, but its superiority has not been convincingly demonstrated yet. This may be due to insufficient focus on behavioural change and development of patients’ self-management skills. Moreover, potentially beneficial communication methods, such as internet and video consultation, are rarely used. We hypothesise that, when compared to centre-based cardiac rehabilitation, cardiac telerehabilitation using evidence-based behavioural change strategies, modern communication methods and on-demand coaching will result in improved self-management skills and sustainable behavioural change, which translates to higher physical activity levels in a cost-effective way.

**Methods:**

This randomised controlled trial compares cardiac telerehabilitation with centre-based cardiac rehabilitation in patients with coronary artery disease. We randomise 300 patients entering cardiac rehabilitation to centre-based cardiac rehabilitation (control group) or cardiac telerehabilitation (intervention group). The core component of the intervention is a patient-centred web application, which enables patients to adjust rehabilitation goals, inspect training and physical activity data, share data with other caregivers and to use video consultation. After six supervised training sessions, the intervention group continues exercise training at home, wearing an accelerometer and heart rate monitor. In addition, physical activity levels are assessed by the accelerometer for four days per week. Patients upload training and physical activity data weekly and receive feedback through video consultation once a week. After completion of the rehabilitation programme, on-demand coaching is performed when training adherence or physical activity levels decline with 50% or more. The primary outcome measure is physical activity level, assessed at baseline, three months and twelve months, and is calculated from accelerometer and heart rate data. Secondary outcome measures include physical fitness, quality of life, anxiety and depression, patient empowerment, patient satisfaction and cost-effectiveness.

**Discussion:**

This study is one of the first studies evaluating effects and costs of a cardiac telerehabilitation intervention comprising a combination of modern technology and evidence-based behavioural change strategies including relapse prevention. We hypothesise that this intervention has superior effects on exercise behaviour without exceeding the costs of a traditional centre-based intervention.

**Trial registration:**

Netherlands Trial Register NTR5156. Registered 22 April 2015.

**Electronic supplementary material:**

The online version of this article (doi:10.1186/s12872-017-0477-6) contains supplementary material, which is available to authorized users.

## Background

Cardiac rehabilitation (CR) has proven beneficial effects on morbidity and mortality, and is highly recommended in clinical guidelines for patients with coronary artery disease (CAD) [1–4]. Unfortunately, CR is vastly underutilised, due to low referral rates and patient-related factors such as travelling distance, work, or social obligations [5, 6]. In addition, improvements in lifestyle behaviour are often not maintained over time. As such, physical activity levels often decline after a successful rehabilitation programme and a significant amount of patients with CAD do not meet the targets for secondary prevention of cardiovascular disease (lifestyle, risk factor and therapeutic targets) [7–9].

Alternatives for current centre-based CR should not only aim to improve uptake rates, but also to maintain the beneficial effects in the long term. For this purpose, it may be effective to shift (part of) the rehabilitation programme to the home environment, especially for patients who are unable to participate in conventional centre-based CR due to transport difficulties or work resumption. A meta-analysis showed no difference between home-based and centre-based CR in mortality risk, cardiac events, improvement of exercise capacity and modifiable risk factors [10]. However, these home-based interventions often lack long-term follow-up and applied varying monitoring strategies and training protocols in heterogeneous study populations. Studies that do report long-term effects showed inconsistent results. A study by Smith et al. showed a decline in peakVO_2_ between one and six years follow-up in both the home-based and hospital-based group, but the rate of decline was significantly smaller in the home-based group [11]. Dracup et al. showed a decline in peakVO_2_ after an initial improvement in patients with heart failure following a home-based walking programme and resistance training [12]. A decline in functional performance might be explained by the fact that these home-based interventions did not primarily focus on behavioural change or on development of self-management skills but on exercise training. In fact, behavioural aspects such as dietary intake and activity behaviour were not monitored.

A more comprehensive approach is provided by cardiac telerehabilitation, which often incorporates multiple components of CR and uses monitoring devices and remote communication with patients to deliver CR outside the hospital environment. Providing objective feedback and allowing patients to track their own progress may increase patients’ self-management skills and thus establish a sustainable behavioural change [13–15]. Two recent systematic reviews reported that, compared to centre-based CR, telerehabilitation resulted in fewer adverse events and rehospitalisation, higher physical activity levels, better adherence to physical activity guidelines, and improved LDL-cholesterol and diastolic blood pressure levels [16, 17]. However, two other systematic reviews showed no differences in outcomes in mortality or modifiable risk factors [18, 19]. The majority of telerehabilitation interventions for cardiac patients are telephone-based interventions, while other methods of communication (e.g. internet, video consultation and/or text messages) may enhance the provision of objective feedback [20]. Furthermore, the effectiveness of internet-based behavioural change interventions increases when one or more multiple behaviour change techniques are applied [20, 21]. For instance, relapse prevention is a cognitive behavioural strategy that can be used in (internet-based) behavioural change interventions such as cardiac telerehabilitation. Relapse prevention teaches an individual how to identify and cope with situations in which the actual behaviour deviates from the intended behaviour. It can be applied to multiple treatment modules in telerehabilitation (e.g. nutritional counselling, smoking cessation or physical activity coaching). Other strategies include goal setting, self-monitoring, provision of feedback, enhancement of self-efficacy and motivational interviewing [22]. If these techniques are implemented, we expect that they will lead to a more sustainable improvement of cardiovascular risk profiles.

We hypothesize that cardiac telerehabilitation using modern communication methods and multiple evidence-based behavioural change strategies including relapse prevention, will result in improved self-management skills and sustainable behavioural change. We expect this will translate to a superior increase in physical activity levels when compared to centre-based CR. Therefore, the objective of the SmartCare-CAD trial is to investigate whether cardiac telerehabilitation using modern technology and multiple behavioural change strategies results in better long-term physical activity levels than centre-based CR in patients with CAD. For telerehabilitation, a personalised patient-centred web application is used, comprising remote monitoring of exercise and physical activity behaviour and on-demand video consultation. In addition, both strategies will be compared with respect to physical fitness, modifiable cardiovascular risk factors, quality of life, anxiety and depression disorders, patient empowerment, patient satisfaction and cost effectiveness.

## Methods

### Study design

This study is designed as a monocentre randomised controlled trial at Máxima Medical Centre Eindhoven/Veldhoven, the Netherlands. Patients from both Máxima Medical Centre and Catharina Hospital Eindhoven are included in the trial. Three hundred patients with CAD entering outpatient CR are randomly allocated to cardiac telerehabilitation with home-based exercise training (intervention group) or centre-based CR (control group). All subjects are requested to provide written informed consent before study entry. Data are collected at baseline and after three, six, nine, and twelve months. The protocol for this study was approved by the Institutional Review Board of Máxima Medical Centre Veldhoven in the Netherlands. The trial is registered at the Netherlands Trial Registry (NTR) with registration number NTR5156. A completed SPIRIT (Additional file 1: Standard Protocol Items: Recommendations for Interventional Trials) diagram can be found in Table 1.

**Table 1 Tab1:**
[figure not shown]
Completed SPIRIT diagram for SmartCare-CAD

* t_1_ = three months, t_2_ = six months, t_3_ = nine months, t_4_ = twelve months

** Three months

** Three months + nine months of on-demand coaching

**** Part of routine care and therefore assessed before informed consent

*KVL-H* Kwaliteit van Leven bij Hartpatiënten, *GAD-7* Generalized Anxiety Disorder, *PHQ* Patient Health Questionnaire, *PAM* Patient Activation Measure, *SBSQ-D* Set of Brief Screening Questions – Dutch, *CQI* Consumer Quality Index

### Study population

Patients entering outpatient CR because of CAD are considered for participation; i.e., patients with stable CAD, an acute coronary syndrome (with or without ST-segment elevation) and/or after coronary revascularization (primary or elective percutaneous coronary intervention (PCI) or coronary artery bypass grafting (CABG)). Only patients referred to exercise training as a part of outpatient CR, based on the individual needs assessment from the guidelines on outpatient CR of the Dutch Society of Cardiology, are asked to participate [23]. Eligible patients are at least 18 years old and have access to a personal computer with Internet connectivity at home. Patients are required to have a mobile phone with short message service (SMS) functionality to login to the web application with two-factor authentication. Patients that do not have a personal computer can be provided with a tablet that has necessary software pre-installed. Exclusion criteria are: 1) ventricular arrhythmia or myocardial ischemia during low to moderate exercise intensity as assessed by symptom limited exercise testing at baseline; 2) heart failure NYHA (New York Heart Association) class IV, and 3) comorbidity precluding exercise training (e.g. orthopaedic, neurological or cognitive conditions). A complete list of inclusion and exclusion criteria is provided in Table 2.

**Table 2 Tab2:** Inclusion and exclusion criteria for SmartCare-CAD

Inclusion criteria	
i.	Referral for cardiac rehabilitation due to stable angina pectoris, acute coronary syndrome (with or without ST-segment elevation) or after coronary revascularization, i.e. (primary or elective) PCI or CABG
ii.	Indication for exercise training as a part of outpatient cardiac rehabilitation
iii.	Personal computer with internet access at home
iv.	Possession of a mobile phone with SMS-functionality
v.	Age ≥18 years
vi.	Able to speak, read and write Dutch
Exclusion criteria	
i.	Ventricular arrhythmia or myocardial ischemia during low to moderate exercise intensity as assessed by symptom limited exercise testing at baseline
ii.	Heart failure NYHA class IV
iii.	Comorbidity precluding exercise training (e.g. orthopaedic, neurological or cognitive conditions)

*PCI* percutaneous coronary intervention, *CABG* coronary artery bypass grafting, *SMS* Short Message Service, *NYHA* New York Heart Association

### Randomisation, blinding and treatment allocation

Patients are randomly allocated to the intervention or control group after baseline measurements by the investigator using a computerised randomisation system in the web-based database software Castor EDC (Castor Electronic Data Capture, Ciwit BV, Amsterdam, The Netherlands), in which block randomisation with variable block size (4, 6 or 8) is applied. Randomisation is stratified for gender and left ventricular ejection fraction (LVEF ≤ 35% or LVEF > 35%) to ensure balance of the treatment arms with respect to the combinations of the prognostic variables. The investigator, supervising healthcare professionals and patients are not blinded for treatment due to the nature of the intervention.

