### Sample size calculation

Adopted from Kraal et. al [24], we calculated sample size for the primary outcome measure –physical activity energy expenditure (PAEE) – assuming PAEE in healthy subjects was 4.0 ± 1.2 MJ/day [25]. If the difference in the primary outcome measure between the intervention and control groups is 10%, 143 subjects need to be included in either group (power = 0.8 and alpha =0.05). Taking into account loss to follow-up, 150 subjects are included in both groups.

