### Outcome measures

The primary outcome measure is physical activity level, assessed at baseline, three months and twelve months. Secondary outcome measures are physical fitness, Body Mass Index (BMI), blood pressure, health related quality of life, anxiety and depression and patient empowerment, assessed at baseline and at three and twelve months. Other secondary outcome measures include patient satisfaction (assessed at twelve months) and cost-effectiveness (assessed at three, six, nine and twelve months). Health literacy is only assessed at baseline. An overview of the study design is provided in Fig. 1.

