### Statistical analysis

All analyses will be performed on an intention-to-treat basis. Descriptive statistics will be used to report demographics and baseline characteristics. Between-group differences and within group differences in the outcome measures will be evaluated using multivariate analysis of variance (MANOVA). Pearson’s correlation coefficient (r) will be applied to quantify relations between changes in variables. For all statistical comparisons, the level of significance will be set at p < 0.05. Analyses will be carried out in the statistical software package SPSS (version 22).

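### Free improvement: the named MANOVA has no term for the stratification factors and does not use baseline PAEE as a covariate, which costs precision but not validity

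*Protocol article*

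**What the plan says.** Protocol article, Randomisation, blinding and treatment allocation: "Randomisation is stratified for gender and left ventricular ejection fraction (LVEF ≤ 35% or LVEF > 35"%). The same sentence describes the factors as prognostic, and the section places allocation after the baseline measurements.

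Outcome measures: "The primary outcome measure is physical activity level, assessed at baseline, three months and twelve months". The Measurements section derives physical activity level from PAEE.

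Statistical analysis: "Between-group differences and within group differences in the outcome measures will be evaluated using multivariate analysis of variance (MANOVA"). No covariate and no stratification factor is named, and the section does not say what role the baseline value plays.

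Sample size calculation: the inputs are "assuming PAEE in healthy subjects was 4.0 ± 1.2 MJ/day", "If the difference in the primary outcome measure between the intervention and control groups is 10"% and "power = 0.8 and alpha =0.05". The result is "143 subjects need to be included in either group", raised to 150 for loss to follow-up.

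**The concern.** The design and the named analysis do not match. Randomisation is restricted on two factors that the protocol itself regards as prognostic, yet the named model has no term for them. Their variance therefore stays in the error term, although the design has already removed it from the real variability of the treatment difference.

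The primary outcome is also measured before allocation, and its baseline value is usually the strongest predictor of its later value. MANOVA as named does not use it as a covariate. Because the plan also asks for within-group differences, baseline is most naturally one of the repeated responses. The treatment effect is then a group-by-time contrast built on changes from baseline. When baseline and follow-up correlate weakly, such a contrast carries more noise than an analysis that conditions on baseline.

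What is at stake is precision that could be had from data already collected. It is not the validity of the test.

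**Working it through.** **Inputs from the Sample size calculation section.** Mean 4.0 and SD 1.2 MJ/day; difference 10% of 4.0 = 0.4 MJ/day, so 0.4/1.2 = 0.333 SD; alpha 0.05; power 0.80; 143 per group. The section does not state sidedness. Two-sided reproduces the figure; one-sided would give 112.

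**Inputs that the document does not give, so assumed.** The correlation r between baseline and follow-up PAEE (0.3, 0.5, 0.7), and the share R² of PAEE variance explained by gender and LVEF stratum (0.02 to 0.10).

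**1. Reproduce the stated figure.** Normal approximation: n = 2 × (1.960 + 0.842)² × (1.2/0.4)² = 141.3, so 142. The exact t calculation gives power 0.799 at 142 and 0.802 at 143, so 143. The trial was thus sized for an unadjusted two-group comparison on the raw SD, and that comparison has its stated 80% power. Its standard error is 1.2 × √(2/143) = 0.142 MJ/day.

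**2. One follow-up visit with baseline as covariate.** The residual SD is 1.2 × √(1 − r²).

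| r | residual SD | SE at 143 per arm | power |
|---|---|---|---|
| 0.3 | 1.145 | 0.135 | 0.84 |
| 0.5 | 1.039 | 0.123 | 0.90 |
| 0.7 | 0.857 | 0.101 | 0.98 |

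**3. MANOVA with baseline as a response: the 2-df group-by-time test.** Assume compound symmetry and 0.4 MJ/day at both 3 and 12 months. The two changes from baseline have covariance 1.2² × (1 − r) × [[2, 1], [1, 2]]. The noncentrality is (143/2) × (2/3) × 0.4² / (1.2² × (1 − r)) = 5.30/(1 − r), referred to F with 2 and 283 degrees of freedom.

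| r | noncentrality | power | baseline as covariate (step 2) |
|---|---|---|---|
| 0.3 | 7.57 | 0.69 | 0.84 |
| 0.5 | 10.59 | 0.83 | 0.90 |
| 0.7 | 17.65 | 0.97 | 0.98 |

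The loss is about 15, 7 and 1 percentage points. If the effect at 3 months is only half of that at 12 months, the group-by-time power falls to 0.55, 0.71 and 0.91. The single-visit comparison at 12 months is unchanged.

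**4. Strata left out of a follow-up comparison.** After stratified randomisation the true SE is 0.142 × √(1 − R²), while the unadjusted model reports 0.142. True two-sided alpha = 2 × [1 − Φ(1.960/√(1 − R²))].

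| R² | true SE | true alpha | power without strata | power with strata |
|---|---|---|---|---|
| 0.02 | 0.140 | 0.048 | 0.807 | 0.813 |
| 0.05 | 0.138 | 0.044 | 0.811 | 0.824 |
| 0.10 | 0.135 | 0.039 | 0.817 | 0.844 |

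The gain from the strata alone is about 1 to 3 points of power.

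**The case against.** The strongest reply is that the article's Statistical analysis section is a short summary naming a family of methods, and that covariates are commonly left to an analysis plan. That limits the point but does not remove it. The section does not defer the choice of model; it names one, and baseline cannot be a covariate in a MANOVA unless the model becomes a MANCOVA or ANCOVA. It remains true that the article nowhere rules covariates out.

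Four stronger readings might be inferred, and the document supports none of them.

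- *That baseline PAEE is ignored.* Baseline is a listed assessment of the primary outcome, and a within-group difference needs it. It is probably a repeated response.
- *That the trial is underpowered for this reason.* The planned unadjusted comparison reaches 80%. Falling below that needs a particular contrast together with an unfavourable assumption, such as a low correlation or a smaller effect at 3 months.
- *That the tests are invalid.* Omitting the strata makes the test conservative. There is no bias and no excess of false positives.
- *That the two losses add up.* They belong to different analyses. In a group-by-time contrast, a gender or LVEF effect that is constant over time cancels within the patient, so step 4 does not apply there.

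Nor is every form of MANOVA weaker than the single-visit covariate analysis. With an equal effect at both follow-ups, a 3-df test of all three visits jointly has power 0.90, 0.93 and 0.98 at r = 0.3, 0.5 and 0.7, because it draws on both follow-ups. But it asks whether the groups differ at any visit, baseline included, not whether they differ in the long term. With an effect at 12 months only, it has 0.72, 0.83 and 0.96, against 0.84, 0.90 and 0.98 with baseline as covariate.

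**Conclusion.** The point holds as a free improvement. The named analysis omits the stratification factors and does not use baseline PAEE as a covariate. Under the most natural reading, the group-by-time test, this costs about 15 points of power at r = 0.3, 7 at r = 0.5 and 1 at r = 0.7. These figures rest on compound symmetry, 0.4 MJ/day at both follow-ups, 143 per arm and the assumed correlations. Most of the possible gain comes from baseline. The strata matter little: if they explain 2% to 10% of the variance, a follow-up comparison without them runs at a true alpha of about 0.048 to 0.039. Since the document gives neither the correlation nor the variance explained, the direction is firmer than the size. The consequence is lost efficiency only.

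**What to change.** In the Statistical analysis section, make the primary analysis a between-group comparison of 12-month PAEE with baseline PAEE, gender and LVEF stratum (≤35% / >35%) as covariates. Analyse each secondary outcome that is measured at baseline in the same way, with its own baseline value. The Randomisation section needs no change; stratifying on these factors is sound.

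The cost is a change of wording. All the covariates are collected before randomisation, so no visit, measurement, design feature or sample size changes. The 143 per group can stand as a calculation without allowance for adjustment.

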### Sample size calculation

Adopted from Kraal et. al [24], we calculated sample size for the primary outcome measure –physical activity energy expenditure (PAEE) – assuming PAEE in healthy subjects was 4.0 ± 1.2 MJ/day [25]. If the difference in the primary outcome measure between the intervention and control groups is 10%, 143 subjects need to be included in either group (power = 0.8 and alpha =0.05). Taking into account loss to follow-up, 150 subjects are included in both groups.

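### The 143 per arm is correct, but its 80% power needs at most 4.67% loss at 12 months and an SD/mean of 0.30 or less in CAD patients; the article supports neither, and baseline adjustment would protect the power at no extra recruitment.

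*Protocol article*

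**What the plan says.** The section on sample size calculation in the Protocol article rests on PAEE, "assuming PAEE in healthy subjects was 4.0 ± 1.2 MJ/day", and on a 10% difference between the groups. From this it concludes "143 subjects need to be included in either group (power = 0.8 and alpha =0.05"). The step to the randomised number is one sentence: "Taking into account loss to follow-up, 150 subjects are included in both groups". No expected loss rate is given, and no reason why healthy-subject values carry over to the trial's patients.

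The section on study population describes different people: "Patients entering outpatient CR because of CAD are considered for participation". The sections on outcome measures and physical activity level place the primary outcome at baseline, three and twelve months. Each assessment needs four days of wear, two of them weekend days, with an accelerometer and a chest-strap heart rate monitor.

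On analysis, the section on statistical analysis says "Between-group differences and within group differences in the outcome measures will be evaluated using multivariate analysis of variance (MANOVA"). It does not mention adjustment for the baseline value.

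**The concern.** Two inputs decide whether 143 evaluable patients per arm give 80% power: how many of the 150 reach the 12-month comparison with usable data, and how variable PAEE is relative to its mean in these patients. The margin on the first is seven patients per arm, to cover a year of follow-up and incomplete sensor recordings. The second is borrowed from a healthy population.

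This is a superiority trial with a long-term aim. If it ends without a significant difference, readers will weigh that result against the stated power. If either input is optimistic, the result is less informative than the stated figure suggests, and the difference the trial could detect is larger than stated.

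**Working it through.** **Inputs from the article.** Mean 4.0 and SD 1.2 MJ/day; difference 10%, so 0.10 × 4.0 = 0.4 MJ/day; alpha 0.05; power 0.80; 150 randomised per arm. The article does not state whether the test is one- or two-sided. Two-sided reproduces its figure and one-sided does not (112 per arm).

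**1. Reproducing 143.** The standardised difference is 0.4/1.2 = 0.333.
- Normal approximation: n = 2 × [(1.960 + 0.842) × 1.2/0.4]² = 141.3, so 142 per arm.
- Two-sample t-test (noncentral t): n = 142.2, so 143 per arm. Power is 0.802 at 143 and 0.799 at 142.

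The article's number is the t-test result. All power figures below use that test.

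**2. The loss allowance.** (150 − 143)/150 = 7/150 = 4.67%.

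**3. Power when loss is larger.** Difference 0.4, SD 1.2. The loss rates are assumptions. The last column is the difference detectable with 80% power.

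| Loss | Evaluable per arm | Power | Detectable difference (MJ/day) |
|---|---|---|---|
| 0% | 150 | 0.821 | 0.39 |
| 4.67% | 143 | 0.802 | 0.40 |
| 10% | 135 | 0.779 | 0.41 |
| 15% | 127 | 0.754 | 0.42 |
| 20% | 120 | 0.730 | 0.44 |

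**4. The healthy-subject mean and SD.** For a relative difference of 10%, the standardised difference is 0.10 × mean/SD. Power therefore depends only on the ratio SD/mean, which the article sets at 1.2/4.0 = 0.30. With 143 evaluable per arm (mean and SD pairs assumed):

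| Mean, SD (MJ/day) | SD/mean | Power |
|---|---|---|
| 3.5, 1.0 | 0.286 | 0.839 |
| 3.0, 0.9 | 0.300 | 0.802 |
| 3.6, 1.2 | 0.333 | 0.715 |
| 4.0, 1.4 | 0.350 | 0.673 |

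A lower mean does no harm to power if the SD falls in proportion. What matters is whether the ratio exceeds 0.30.

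**5. What baseline adjustment gives.** If baseline and 12-month PAEE correlate at r, adjusting for baseline reduces the SD to 1.2 × √(1 − r²). At 20% loss (120 per arm), difference 0.4, r assumed:

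| r | Residual SD | Power |
|---|---|---|
| 0 (unadjusted) | 1.200 | 0.730 |
| 0.3 | 1.145 | 0.769 |
| 0.4 | 1.100 | 0.801 |
| 0.5 | 1.039 | 0.844 |
| 0.6 | 0.960 | 0.895 |

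A correlation of about 0.40 is enough to bring power back to 80% at 20% loss.

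**The case against.** Nothing in the calculation is wrong. The 143 is exact, and a small allowance for loss is still an allowance. The article condenses a fuller protocol and takes its inputs from cited studies that are not shown, so a justification may exist elsewhere. Loss of 10% costs only about two points of power. All of this stands, and it is why the point concerns the support for the inputs and not the arithmetic.

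Three stronger readings are tempting, and the documents support none of them.

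- A reader might infer that 80% power requires coronary patients to have the same mean and SD as healthy subjects. It does not: step 4 shows that any ratio of 0.30 or less suffices, and a smaller ratio raises power.
- A reader might infer that the trial is underpowered. The article contains neither an observed loss rate nor a patient mean or SD, so a shortfall is possible and not demonstrated.
- A reader might infer that the planned MANOVA drops every patient with one missed assessment. The section on statistical analysis specifies neither the set of dependent variables nor the handling of missing data, and it states intention to treat. Such details are commonly left to an analysis plan, and their absence here is not an error.

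It is also fair to say that the 4.67% limit belongs to an unadjusted comparison at one time point. The article does not say how baseline enters the MANOVA, so the power of the stated analysis cannot be computed from it.

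**Conclusion.** The concern holds in a limited form. The sample size is arithmetically correct, but its 80% power is conditional on two things that the article does not support: loss of no more than 4.67%, counting missing sensor data, and an SD/mean of 0.30 or less in coronary patients. Over the assumed ranges, power is 78% to 73% for loss of 10% to 20%, and 72% to 67% for a ratio of 0.333 to 0.35 at 143 per arm. Ratios below 0.30 move power the other way.

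These figures assume a two-sided, unadjusted two-sample t-test at 12 months, the time point that matches the long-term objective. The practical consequence is that the trial can buy a real margin from data it already collects. Adjustment for baseline PAEE offsets 20% loss if the correlation with the 12-month value is about 0.40 or more. That correlation is not in the article either.

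**What to change.** Two changes, neither of which requires more patients.

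1. In the section on statistical analysis, define the primary between-group comparison as PAEE at 12 months in a model adjusted for baseline PAEE, in place of a MANOVA with no stated baseline adjustment. Baseline is measured before randomisation, so the covariate is already available.
2. In the section on sample size calculation, state the implied loss allowance of 4.67%. Restate the detectable difference in MJ/day using the pooled, arm-masked baseline mean and SD of the patients enrolled since May 2016, across a range of loss such as 10% to 20%. Say explicitly that this assumes the 12-month SD is similar to the baseline SD.

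The cost is a paragraph of text and one masked calculation on data in hand. The downside is that the stated power or detectable difference may become slightly less favourable. The change should be made before any outcome data are seen by arm.
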